## Abstract

**Background:**

Alcohol use disorder (AUD) poses a significant global health challenge. Traditional management strategies often face high relapse rates, leading to a need for innovative approaches. Mindfulness-based relapse prevention (MBRP) has emerged as a promising intervention to enhance cognitive control, reduce cue-related craving and improve interoceptive processing. Neuroimaging studies suggest that mindfulness training can modulate brain networks associated with these factors, potentially improving treatment outcomes for AUD. Neuroimaging studies suggest that mindfulness training can modulate brain networks linked to these brain functions, potentially improving treatment outcomes for AUD. However, it is unclear how MBRP links to neurophysiological measures such as frontal midline theta oscillations (FMΘ) and whether the beneficial effects of MBRP can be increased by enhancing FMΘ. Here, we will use two different forms of neuromodulation to target and enhance these oscillations, and evaluate their impact on the effectiveness of MBRP.

**Methods:**

This study will employ a four-arm randomized controlled trial to evaluate the synergistic effects of MBRP augmented with transcutaneous vagus nerve stimulation (tVNS) or closed-loop amplitude-modulated transcranial alternating current stimulation (CLAM-tACS) on cognitive control, cue reactivity and interoceptive processing in AUD patients. Participants will undergo six weekly group MBRP sessions and daily individual mindfulness practices. Assessments will include an inhibition task, cue-induced craving task, and heartbeat discrimination task, alongside heart rate variability and 32-channel EEG recordings. Participants will be assessed pre and post treatment, with a three-month follow-up to evaluate long-term effects on abstinence and alcohol consumption.

**Discussion:**

This study will not only elucidate the causal link between FMΘ and efficacy of MBRP, but contribute to a better understanding of how combined psychological and neuromodulation interventions can improve treatment outcomes for AUD, potentially leading to more effective therapeutic strategies. This study also seeks to explore individual differences in response to treatment, which could inform future approaches to AUD management.

**Trial registration:**

This study received approval by the Charité—Universitätsmedizin Berlin Institutional Review Board (EA1/030/23, 10.11.2023). It was registered on ClinicalTrials.gov (NCT06308484).

## Background

Alcohol use disorder (AUD) is a significant global health concern, contributing to about 5% of the global disease burden, with an estimated 3.8% of global deaths attributable to it [1, 2]. Despite its prevalence, with 12-month rates ranging from 5 to 14% [3], AUD management faces considerable unmet clinical needs. It remains one of the most under-treated psychiatric disorders globally, with treatment coverage estimated at 10–20% [4]. A meta-analysis found that only up to 50% of individuals with AUD achieve remission over several years [5]. In response to the challenge of high relapse rates, innovative approaches such as mindfulness-based relapse prevention (MBRP) have emerged. MBRP integrates core aspects of relapse prevention with techniques adapted from mindfulness-based stress reduction (MBSR) and mindfulness-based cognitive therapy (MBCT) [6, 7]. At the core of MBRP lies the emphasis on identifying high-risk situations, training participants to recognize early warning signs for relapse, enhancing awareness of internal and external cues associated with substance use, developing effective coping skills, and boosting self-efficacy [8]. These strategies directly address the mechanisms underlying addiction, such as cue reactivity, loss of cognitive control, and impairment of interoceptive processing, as highlighted in numerous studies [9, 10].

The neuronal correlates of these mechanisms have been explored by means of neuroimaging such as functional magnetic resonance imaging (fMRI) and electroencephalography (EEG). Research has shown that MBRP and similar mindfulness-based interventions (MBIs) were found to increase resting state connectivity between the default mode network and prefrontal regions that contribute to cognitive control [11, 12]. In addition, after brief MBI, enhanced prefrontal activation during an executive attention task as well as increased glutamate metabolism in the anterior cingulate cortex (ACC) were observed [13, 14]. MBI also positively influenced behavioral inhibition, which correlated with enhanced conflict and response monitoring as indicated by neurophysiological EEG measurements [15, 16]. Additionally, MBIs have been effective in altering addiction-related attentional biases in individuals with alcohol use disorder [17].

In line with these findings, studies have observed decreased neuronal activation in response to drug-related cues in brain regions associated with cue reactivity such as the medial prefrontal cortex (PFC) and ventral striatum (VS) [18, 19]. Consistent with these results, altered functional connectivity in neurocircuitry related to craving such as between the insula and the VS has been found [20]. Functional neuroimaging of the effects of MBIs thus points towards a modulation of striatal cue reactivity, possibly through engagement of prefrontal control processes that result in reduced craving. Indeed, this lines up with results in an AUD cohort, showing that abstinence was positively associated with ACC-striatal connectivity during the presentation of alcohol cues [21].

Further underlining the importance of this brain region, ACC activation has also been linked to the processing of interoceptive cues [22]. The modification of interoception is hypothesized to be an important driver of the efficacy of MBIs [23]. Improved interoceptive processing could foster a more adaptive response to bodily sensations and enhance the capability to recognize and manage craving effectively [9, 24, 25].

Moreover, there is a strong link between frontal midline theta (FMΘ) oscillatory brain activity and MBI-induced increases of cognitive control. In patients with opioid use disorder, increased self-regulatory strength and self-control was indicated by endogenous theta stimulation in the PFC during active mindfulness meditation [26, 27]. FMΘ during behavioral inhibition has been linked to activity of a network that includes, among others, the ACC as well as medial PFC frontal gyrus [28].

Besides MBIs, neurotechnological interventions such as transcutaneous vagus nerve stimulation (tVNS), may improve cognitive control by modulating FMΘ oscillations. In analogy to the effects of mindfulness on neuronal function, it has been suggested that tVNS can modulate activity in prefrontal brain regions associated with cognitive control [29]. In line with this, FMΘ was found to be enhanced under tVNS along with behavioral improvements in executive control [30]. Furthermore, tVNS has been shown to improve measures of interoception [31, 32]. Considering this, tVNS has been suggested as a tool in the treatment of several psychiatric disorders and could be an effective adjunct to psychological modulation of self-regulation/cognitive control such as MBIs. Indeed, tVNS has been proposed to be an effective treatment approach in AUD [33]. Therefore, we reason that augmenting a MBRP program with tVNS could amplify improvements in cognitive function and interoceptive processing along with decreasing cue-associated behavior e.g. craving-associated drug-seeking in AUD.

Although MBI and tVNS have been used to improve cognitive control and inhibit addiction-related behavior by modulating FMΘ, they are not ideal for investigating the causal role of FMΘ in generating such behavior. To causally link FMΘ oscillations to behavior, they should be directly engaged by neuromodulation without relying on unspecific mechanisms [34]. While transcranial magnetic stimulation (TMS) targeting medial prefrontal brain regions can reduce cue-induced craving, TMS is not suitable for frequency-specific neuromodulation [35, 36]. A major challenge in establishing neuromodulation that adapts to ongoing, endogenous brain oscillations is the suppression of stimulation artifacts impeding continuous neurophysiological assessments [37]. By using advanced mathematical approaches [38–40] and stimulation protocols such as amplitude modulation [41], this challenge could be overcome allowing now for frequency- and phase-specific adaptive neuromodulation.

Here, we propose using such approach, specifically closed-loop transcranial alternating current stimulation (CLAM-tACS), to explore the causal role of FMΘ oscillations in addiction-related behavior. CLAM-tACS avoids sensory co-stimulation and allows for the parallel assessment and adaptation of brain oscillations at the target frequency during stimulation [42–45]. This system can enhance or suppress endogenous brain oscillations by adjusting the phase difference between CLAM-tACS and targeted oscillations [43]. Our planned study will use this approach to investigate the causal link between medial prefrontal brain activity and addiction-related behavior by modulating FMΘ oscillations.

In summary, we want to investigate the synergistic effects of MBRP and neuromodulation techniques in the context of AUD. We propose that the previously described addiction-related mechanisms could be targeted on a psychological and neurophysiological level through mindfulness training and neuromodulation. This combination could enhance the efficacy of MBRP and in turn improve the treatment of AUD. In addition, we will investigate the causal role of FMΘ via innovative real-time modification of target oscillations.

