## Methods and analysis

### Study design

We will conduct a four-arm randomized controlled study at the Department of Psychiatry and Neurosciences, Charité – Universitätsmedizin Berlin. Detoxified patients with Alcohol Use Disorder (AUD) will undergo a meticulously structured Mindfulness-Based Relapse Prevention (MBRP) program consisting of six weekly group sessions supplemented with daily individual mindfulness practice sessions. Prior to and following treatment, participants will undergo comprehensive assessments including cognitive control evaluation using a Simon Go/NoGo (SGNG) task, assessment of cue-induced craving and a heartbeat discrimination task (HDT) as a marker for interoception, complemented by electrocardiographic measurements of heart rate and heart rate variability, alongside 32-channel electroencephalography (EEG) recordings. The pre and post treatment assessments will encompass various clinical and psychological metrics, including symptom and craving severity, as well as perceived loneliness and impulsivity. Long-term treatment effects will be evaluated through a follow-up assessment after three months, focusing on abstinence rates and alcohol consumption (Fig. 1).

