### MBRP

Detoxified AUD patients will be enrolled in a rolling format MBRP group therapy that consists of six weekly sessions and daily stand-alone practice of mindfulness techniques (independently performed by the participants between sessions). All participants will receive a psychological one-on-one consultation before start of MBRP to boost motivation to participate as well as convey general information about the structure of the program. MBRP group therapy will be administered by trained staff members and according to manuals by Bowen et al. [62] and Roos et al. [63] that were modified to accommodate six sessions in a rolling format. Further, group leaders receive regular/biweekly/monthly supervision by an experienced group psychologist/supervisor to ensure quality of MBRP group therapy during the study.

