## Discussion

This research project endeavors to enhance the effectiveness of MBRP while advancing treatment options for AUD. The study will delve into the nuanced impact and underlying mechanisms of neurostimulation protocols in conjunction with MBRP. Specifically, we will investigate the potential of tVNS and CLAM-tACS as supplementary treatments without incorporating a control intervention to MBRP. Numerous meta-analyses have highlighted the effectiveness of various mindfulness-based interventions (MBIs) in AUD populations, prompting our exploration into the mechanisms underlying this efficacy [76, 77]. While our study design does not allow for conclusive findings regarding potential disparities in cue reactivity, cognitive control, and interoceptive abilities between AUD individuals and healthy controls, we aim to monitor the potential influence of our intervention on these factors. Additionally, we anticipate that disease severity and treatment efficacy could be predicted based on these factors and their interplay, considering the inherent heterogeneity within AUD populations [78]. Conducting exploratory analyses on individual profiles could significantly contribute to a dimensional conceptualization, thereby facilitating the development of enhanced treatment and prevention strategies.

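### The aim is worded as synergy between MBRP and neuromodulation, but every patient receives MBRP, so the trial can show only the add-on effect of stimulation

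*Protocol article*

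**What the plan says.** **The aim.** The last paragraph of the Background gives the purpose as "we want to investigate the synergistic effects of MBRP and neuromodulation techniques in the context of AUD". The Methods paragraph of the Abstract says the four-arm trial will "evaluate the synergistic effects of MBRP augmented with transcutaneous vagus nerve stimulation (tVNS", and the sentence goes on to name CLAM-tACS as the other stimulation method. The Discussion paragraph of the Abstract adds: "This study will not only elucidate the causal link between FMΘ and efficacy of MBRP".

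**Who receives MBRP.** Under Study design: "Detoxified patients with Alcohol Use Disorder (AUD) will undergo a meticulously structured Mindfulness-Based Relapse Prevention (MBRP) program". Under MBRP: "All participants will receive a psychological one-on-one consultation before start of MBRP". No arm without MBRP is described anywhere. The main Discussion confirms this, saying the study examines "the potential of tVNS and CLAM-tACS as supplementary treatments without incorporating a control intervention to MBRP". It supports the choice by pointing to meta-analyses of mindfulness-based interventions in this population.

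**What is analysed.** Statistical methods and analysis sets the primary comparison as active against sham stimulation on neurobehavioural measures, through a treatment-by-time effect in a linear mixed model. Abstinence and drinking are then compared between sham and active stimulation, with MBRP in both. No contrast between MBRP and no MBRP, and no MBRP-by-stimulation term, is described.

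**The concern.** Synergy is a statement about an interaction: the two treatments together achieve more than their separate effects would give. To show it one must know what stimulation does without MBRP, and this trial has no patients who could supply that.

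The competing explanation is realistic on the article's own account. The Background cites work in which tVNS was followed by better executive control and better interoception, and notes that tVNS has been proposed as a treatment for AUD. Stimulation could therefore help these patients by the same amount whether or not they practise mindfulness. The trial would then show a difference between active and sham, and under the stated aim that difference could be read as synergy although there is none.

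The same gap affects the phrase about the efficacy of MBRP. The trial never estimates that efficacy, so it cannot show that theta activity is what produces it. At stake is what a positive result may be said to mean, not whether the active-versus-sham comparison is valid.

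**Working it through.** No figure in the plan bears on this point, so there is nothing to reproduce. The question is whether the quantity named in the aim can be identified from the design.

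**Inputs.** MBRP is given to all patients (Study design, MBRP, Discussion). The comparison is active against sham (Statistical methods and analysis). The text does not list the four arms. Active and sham tVNS plus active and sham CLAM-tACS is inferred from the sample size and analysis sections. The argument needs only that MBRP is constant, and it applies to each stimulation method separately.

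**Model for one method.** Let M = 1 for MBRP and 0 otherwise, and S = 1 for active and 0 for sham stimulation.

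Mean outcome = b0 + bM·M + bS·S + bMS·(M·S)

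Here bS is the effect of stimulation without MBRP, bM is the effect of MBRP under sham, and bMS is the departure from additivity, which is what synergy means.

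**What the design observes (M = 1 throughout).**
- Sham arm: b0 + bM
- Active arm: b0 + bM + bS + bMS
- Active minus sham: bS + bMS

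**Three situations with the same result.** Call the observed difference D.

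| Situation | bS | bMS | Active minus sham |
|---|---|---|---|
| Independent, additive | D | 0 | D |
| Pure synergy | 0 | D | D |
| Antagonism | 2D | −D | D |

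The data are identical in all three.

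**Rank check.** With columns (1, M, S, M·S), the two observed cells are (1,1,0,0) and (1,1,1,1). The M column equals the intercept and the M·S column equals the S column, so the rank is 2 of 4. A full 2×2 adds (1,0,0,0) and (1,0,1,0) and has rank 4. A larger sample adds copies of the same two rows and leaves the rank at 2.

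**Cost of a design that could test synergy (illustration only).** Assume a two-sided 5% level, 80% power and a standardised difference d = 0.63, about what 40 per group can detect.
- Active versus sham, per arm: 2 × ((1.96 + 0.84)/0.63)², rounded up to 40; total 80.
- Interaction of the same size, per cell: 4 × ((1.96 + 0.84)/0.63)², rounded up to 80; total 4 × 80 = 320.
- Interaction of the same size at d = 0.577: 380 in total. At d = 0.5: 504.
- Interaction half the size of d = 0.63: 317 per cell, 1,268 in total.

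These are evaluable patients for one stimulation method. The plan recruits 140 in total for both.

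**The case against.** The strongest reply is that the article uses *synergistic* loosely. Elsewhere it speaks of augmentation: the Abstract asks whether stimulation can increase the benefit of MBRP, the Background calls tVNS an adjunct, and the Discussion speaks of supplementary treatments. Whether MBRP with active stimulation gives better outcomes than MBRP with sham is a question the design answers. The missing control is also disclosed and justified, and the analysis section already targets the add-on effect.

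Most of this stands. It shows that no analysis is mis-specified and that the remedy is small. It does not remove the point, because the Discussion discloses the missing control without withdrawing or limiting the synergy aim, which appears both in the Abstract and in the closing statement of purpose. Nor is this a detail left to a fuller document: no analysis plan can recover an interaction from a design in which one factor never varies.

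Two stronger readings are tempting, and the document supports neither.
- A reader might infer that the theta aim has no supporting contrast at all. But CLAM-tACS is phase-tuned to the theta rhythm during a mindfulness exercise, and both phase-locking and the change in theta amplitude are to be checked. A randomised active-versus-sham comparison then bears causally on outcomes during MBRP. The Background also states the causal aim more narrowly, as medial prefrontal activity and addiction-related behaviour, which needs no arm without MBRP. Only the Abstract's reference to the efficacy of MBRP goes too far.
- A reader might infer that the plan credits pre-to-post change in the sham arms to MBRP. Nothing in the text does so; the planned effect is treatment by time.

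**Conclusion.** The point holds as a mismatch between the stated aim and what the design can conclude. The trial identifies the effect of active versus sham stimulation in patients who all receive MBRP. It cannot distinguish synergy from an independent additive effect, and it cannot estimate MBRP's own efficacy. The limit is absolute (rank 2 of 4 in the model above), so neither more patients nor a different model would lift it. Changing the scale, for example to ratios of abstinence rates, does not help either, since any definition of synergy needs the stimulation effect without MBRP.

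This rests on reading *synergistic* in its usual sense and on MBRP being given in every arm, which the text supports directly. The figure showing the design was not available, but the finding does not depend on how the four arms are split. The add-on comparison is a sound and useful question; the fault lies in the claim attached to it.

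**What to change.** - In the Abstract (Methods) and the last paragraph of the Background, replace the synergy wording with: *the add-on effect of active versus sham tVNS (or CLAM-tACS) in patients who all receive MBRP*. This agrees with the Discussion's own description of stimulation as supplementary.
- In the Abstract (Discussion), limit the causal statement to: *the effect of theta-targeted stimulation on neurobehavioural and drinking outcomes during MBRP*.
- In the main Discussion, beside the sentence on the missing control, add that synergy between MBRP and stimulation, and the efficacy of MBRP itself, cannot be concluded from this trial.

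Arms, sample size, data collection and analyses stay the same. The only cost is a more modest claim. Keeping the synergy aim instead would require arms without MBRP and, on the illustrative assumptions above, several times as many patients for each stimulation method.

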## Methods and analysis

### Study design

We will conduct a four-arm randomized controlled study at the Department of Psychiatry and Neurosciences, Charité – Universitätsmedizin Berlin. Detoxified patients with Alcohol Use Disorder (AUD) will undergo a meticulously structured Mindfulness-Based Relapse Prevention (MBRP) program consisting of six weekly group sessions supplemented with daily individual mindfulness practice sessions. Prior to and following treatment, participants will undergo comprehensive assessments including cognitive control evaluation using a Simon Go/NoGo (SGNG) task, assessment of cue-induced craving and a heartbeat discrimination task (HDT) as a marker for interoception, complemented by electrocardiographic measurements of heart rate and heart rate variability, alongside 32-channel electroencephalography (EEG) recordings. The pre and post treatment assessments will encompass various clinical and psychological metrics, including symptom and craving severity, as well as perceived loneliness and impulsivity. Long-term treatment effects will be evaluated through a follow-up assessment after three months, focusing on abstinence rates and alcohol consumption (Fig. 1).

**Fig. 1 Fig1:**
[figure not shown]
Graphical study design. Abbreviations: HDT – heartbeat detection task, EEG – electroencephalography, FMΘ – frontal midline theta, MBRP – mindfulness-based relapse prevention, tVNS – transcutaneous vagus nerve simulation, CLAM-tACS – closed-loop amplitude modulated transcranial alternating current stimulation. Image of Simon Go/NoGo task adapted from [46] licenced under CC BY 4.0

### Recruitment

We will recruit patients with AUD in psychiatric clinics (inpatient and outpatient) throughout Berlin and Brandenburg. In addition, we will distribute our study information to support group networks that address patients with AUD. Interested patients will be screened for eligibility by means of a telephone interview.

### Inclusion criteria

ICD-10 diagnosis of alcohol dependence (F10.2) and at least 2 criteria for AUD according to DSM-5 (last 12 months).Completion of in-patient withdrawal treatment and abstinence duration less than 12 months.Ability to understand study information and provision of written informed consent.Age 18–70 years.

